### Sample size calculation:

The sample size calculation for patients with C-peptide negative diabetes type 1 is based on ANCOVA comparing glucagon levels and an expected increase of 30% after glibenclamide treatment and =0.05 using the following formula:

2[Z+Z]2 [s] 2

= N

2

where N is the required sample size, Z and Z are the false positive and false negative error rates tolerates (Z =1.96 (95%, 2 tailed); Z=0.84 (80% 1-tailed), s2 is the variance based on prior studies (square of the standard deviation (SD)) and  is the difference in the primary endpoint (change glucagon levels). The Glucagon level was found to be 22 ± 3 ng/l in patients with diabetes type 1 (13). The sample size will be 8. 10 patients per group will be recruited in order to account for potential drop-outs.

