# Study design and methods:

## General description of the study:

Patients with type 1 diabetes participating in this single-blind, randomized cross-over study evaluating the effect of glibenclamide on glucagon secretion during insulin induced hypoglycemia. Glucose and glucagon metabolism will be studied using an intravenous insulin infusion test. We anticipate that patients diagnosed with C-peptide negative type 1 diabetes will increase glucagon secretion after oral administration of glibenclamide compared to patients with type 1 diabetes with maintained residual -cell function.

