## Statistical Considerations:

### Data analysis:

The primary endpoint for the comparison of patients with diabetes type 1 with and without treatment with glibenclamide will be the area under the curve of plasma glucagon concentrations from time 0 (start of the insulin infusion) to time 150 (150 min after the onset of the insulin infusion).

The secondary endpoint will be the rate of recovery of plasma glucose concentrations from 60 to 150 min, after tapering the insulin infusion to 15 mU/m2/min.

Further secondary endpoints will be the relation of symptoms and signs of hypoglycemia and hypoglycemia awareness to counter-regulatory hormone concentrations during insulin induced hypoglycemia.

The data analysis consists of the analysis of the primary and secondary endpoint. Data will be expressed as means ± SEM, Analysis of variance and appropriate post hoc analysis will be used to assess the effect of glibenclamide therapy over time. Unpaired t-tests and Mann-Withney U-tests will be used to compare baseline parameters between groups.

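### The stated formula and inputs return 4, not 8; the 8 fits only a parallel-arm total, so the stated 80% power is not established for the crossover AUC comparison

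*Protocol*

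**What the plan says.** The protocol's section 'Sample size calculation' covers the C-peptide-negative patients. It says the calculation "is based on ANCOVA comparing glucagon levels and an expected increase of 30% after glibenclamide treatment". It prints the formula 2(Zα + Zβ)²s²/δ² = N and calls N the required sample size, without saying whether that is per arm or in total. It sets two-sided 5% and 80% power through Z values of 1.96 and 0.84, and defines s² as the square of a standard deviation from earlier studies. For the mean and spread it cites one source: "The Glucagon level was found to be 22 ± 3 ng/l in patients with diabetes type 1 (13"). It then concludes: "The sample size will be 8. 10 patients per group will be recruited in order to account for potential drop-outs".

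Three other parts of the protocol bear on this:

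- 'General description of the study' calls the trial a "single-blind, randomized cross-over study". The sections on the randomisation procedure and the second insulin infusion study confirm that every patient takes glibenclamide in one period and placebo in the other.
- 'Data analysis' makes the glucagon AUC from 0 to 150 min the primary endpoint, to be analysed by analysis of variance.
- 'Study objectives' frames the aim as C-peptide-negative compared with C-peptide-positive patients.

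**The concern.** A reader who puts the printed inputs into the printed formula does not get the printed answer. The formula also belongs to another design (independent groups) and another quantity (a glucagon level). A crossover is sized on the SD of the within-patient difference between treatments. The protocol gives neither that SD nor a within-patient correlation, and it gives no mean or SD for the AUC. The calculation is described as ANCOVA, the analysis plan says analysis of variance, and the formula is neither.

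At stake is the trial's only statement of power. If it does not describe the primary comparison, the protocol does not tell a reader what size of effect the trial could be expected to detect.

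**Working it through.** **Inputs from 'Sample size calculation'.** Z values 1.96 and 0.84, mean 22 ng/l, s = 3 ng/l, increase 30%. Applying the 30% to the mean of 22 is an inference: δ = 0.30 × 22 = 6.6 ng/l.

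**1. The plan's figure.**
- N = 2 × (1.96 + 0.84)² × 3² / 6.6² = 2 × 7.84 × 9 / 43.56 = 141.12 / 43.56 = 3.24, rounded up to 4.
- In this formula N is the number per arm. Two parallel arms give 2 × 4 = 8, which matches the stated figure exactly.
- Without doubling, an exact 8 needs s = √(8 × 43.56 / 15.68) = 4.71, or a difference of √(15.68 × 9 / 8) = 4.2 ng/l, which is 19% of 22. Neither is stated.

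**2. What 8 gives on the stated inputs.** The SD of the within-patient difference is s√(2(1 − ρ)). The protocol gives no ρ, so it is varied here. Power is from the noncentral t distribution, two-sided 5%, difference 6.6 ng/l, 8 patients, paired.

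| ρ | SD of difference | Power |
|---|---|---|
| 0 | 4.24 | 96.3% |
| 0.3 | 3.55 | 99.4% |
| 0.5 | 3.00 | 99.9% |

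In the formula's own independent-groups layout, a t-test has 73.7% power with 4 per arm and 98.3% with 8 per arm. Neither layout gives 80% at 8.

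**3. Conditional check: if ± 3 were an SEM.** The source's sample size is not given, so 6 to 10 is assumed. Then SD = 3√6 to 3√10 = 7.3 to 9.5, and the same formula returns 19.4 to 32.4 per arm. Paired power for 6.6 ng/l with 8 completers would be:

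| ρ | Source n = 10 (SD 9.5) | Source n = 6 (SD 7.3) |
|---|---|---|
| 0 | 23% | 34% |
| 0.5 | 40% | 59% |
| 0.8 | 76% | 93% |

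**4. What the fixed enrolment can detect.** Effects detectable with 80% power at two-sided 5%, in SDs of the within-patient AUC difference:

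| Comparison | 8 completers per group | 10 completers per group |
|---|---|---|
| Within group, simple paired t-test | 1.16 | 1.00 |
| C-peptide-negative vs positive, two-sample t-test on the differences | 1.51 | 1.32 |

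The second row assumes equal SDs in the two groups. With a period term, the within-group values become 1.19 (sequences 4/4) and 1.01 (5/5). Randomisation by odd or even random number does not guarantee balance; a 6/2 split among 8 completers gives 1.37.

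**The case against.** The strongest reply is that 8 is not a slip. It is exactly two arms of 4, it needs no unstated number, and it reads naturally as the count of C-peptide-negative patients before the allowance to 10. That stands as the likely origin, so it would be too strong to say that 8 cannot be derived. What remains is that the step is not written down, N is not defined, and a crossover has no second set of patients to add.

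The reply also notes that the error is conservative on the stated inputs. That stands too. A reader might infer from this point that the trial is too small, and the document does not support that inference. Even the between-group contrast of 6.6 ng/l, for which no calculation is given, would have 82% power with 8 per group at ρ = 0, assuming SD 3 in both groups and no change in C-peptide-positive patients.

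A reader might also infer that ± 3 is an SEM, because 'Data analysis' says "Data will be expressed as means ± SEM". That sentence governs how this trial will report its own data and says nothing about how the cited source reported. The sample size paragraph defines s² through an SD and then supplies ± 3. The low power figures therefore rest on an unproven reading, an assumed source size and an assumed correlation.

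Finally, AUC over 150 min is the time-averaged level times 150, so a 30% rise in mean level is a 30% rise in AUC. The effect size can carry over. The SD of a level cannot stand in for the SD of the within-patient AUC difference, and that part of the criticism is not answered. Nor would a null result become uninterpretable: a confidence interval would still show which effects are compatible with the data.

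**Conclusion.** The paragraph is wrong as written. Its formula and inputs return 3.24, i.e. 4. The stated 8 comes from an unstated doubling that does not apply to this crossover, and the SD is not that of the primary comparison. The 80% power is not established for the AUC endpoint, and it cannot be recomputed because the protocol gives no AUC mean or SD.

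On the stated inputs the discrepancy is in the safe direction: at least 96% paired power with 8 completers, taking 3 as the between-patient SD, a true difference of 6.6 ng/l and ρ ≥ 0. Under-enrolment is not shown. Whether ± 3 is an SD or an SEM is a question to put to the sponsor; the SEM scenario holds only under its assumptions. The point deserves correction but does not call the trial's size into question.

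**What to change.** Replace the sample size paragraph and leave enrolment at 10 per group:

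- Define N as patients in the crossover, each contributing both periods, and drop 8 as the result of this formula.
- Confirm from the cited source whether ± 3 is an SD or an SEM, and label it.
- Name the comparison that is powered: the treatment effect within C-peptide-negative patients, or the contrast between C-peptide groups in 'Study objectives'.
- State what the fixed enrolment detects on the AUC at 80% power and two-sided 5%. Within group this is 1.16 SD (8 completers) or 1.00 SD (10) of the within-patient difference by simple paired t-test, and somewhat more with a period term or unbalanced sequences. Between groups it is 1.51 or 1.32 SD.
- Translate these into percentage changes over a stated range of SD and within-patient correlation, since SD units alone mean little clinically.
- Align the named method (ANCOVA or analysis of variance) with 'Data analysis'.

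The cost is one rewritten paragraph and a check of one source, with no extra patients. The downside is that the stated detectable effect may look less favourable, particularly if ± 3 proves to be an SEM.

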# Organisation:

## Specific Location:

Outpatient Clinic, Division of Endocrinology, Diabetes and Clinical Nutrition, University Hospital Basel, Klinikum 2, [name], Basel, Switzerland

Clinical Research Center, University Hospital Basel, Klinikum 2, [name], Basel, Switzerland.

## Time schedule:

Start of the study: March 2007

Duration: 9 months including recruitment period.

# Informed Consent, Ethical Review, Liability, Regulatory and Economic Considerations:

## Informed consent:

Subjects are required to provide written informed consent before enrollment into the study protocol. The consent includes a statement that enrolled subjects agree on the use of their data for scientific purposes. Patients who are not able to give written informed consent are not included in the study. The informed consent document will be used to explain in simple terms the aim of the study, required visits and procedures. The informed consent document contains a statement that the consent is freely given, and that the patient is free to withdraw from the study at any time.

## Ethical review:

This protocol will be submitted for approval to the conjoined local ethic committee of Basel and Baselland and to Swissmedic for approval of the use of glibenclamide (Daonil®) and placebo pills.

## Liability:

The study procedures will be covered by the general liability insurance RIMAS* of the University Hospital Basel, as will be certified by [name] (Rechtsdienst, University Hospital Basel).

(* RIMAS, Insurance-Broker AG, [name], [name], [contact], [contact]).

## Regulatory Considerations:

This study will be conducted in accordance with the ethical principles stated in the most recent version of the Declaration of Helsinki or the applicable International Conference on Harmonization (ICH) guidelines on good clinical practice, whichever represents the greater protection of the individual.

The study will not be started until approval of the study protocol by the local ethical committee and Swissmedic.

Data collected will be kept confidential and accessible only to researchers involved, the ethical review committee and Swissmedic. The data records will be stored in a locked room and the electronic data will be kept on a computer with password protection. All study records will be kept for at least 15 years.

## Economic Considerations:

No additional costs will arise through participation in the study, i.e. there are no cost to the patients or their health insurance. There will be no charges for any of the testing procedures during the study. Patients will be paid a total of CHF 250 .- for each completed inpatient study, i.e. a total of CHF 500.- for patients completing the study per protocol. Patients not eligible to participate based on the results of the screening visit will receive no imbursement.

The salary of [name] is provided by the Lichtenstein-Stiftung Basel, Switzerland. Further financial support will be requested from the “Diabetesstiftung der Region Basel” and the “Wissenschaftlicher Kredit des Universitätsspitals Basel” and the Novartis-Fonds at the University Hospital Basel.

